##### Exclusion criteria

Female (FACT OBS only), Cancer (FACT INT only), Habitual consumers of a diet high in NSP and RS, Smokers, Type 2 diabetics, Dieters, Inflammatory Bowel Disease.

#### High Fibre intervention

The primary goal of the intervention arm is to elevate colonic SCFA levels, which will be monitored through analysis of faecal SCFA. Elevation of fermentable fibre intake is a rapid and amenable mechanism to achieve this goal. Patients recruited to the FACT INT arm will be offered a range of high-fibre foods, including switch to wholemeal bread, fruit, dried fruit snacks, from a basket of options identified by the research team (Additional File 1). Foods will be ordered by the researcher and delivered by a supermarket home delivery to the patients' homes. Compliance will be estimated and supported through interim telephone calls and 24 hr recall estimates.

#### Primary outcome measure

##### Development of a methodology for studying global protein acetylation in biopsy samples and proof of principle studies

It is the goal of this study to link alterations in global proteins acetylation in the colon mucosa to levels of butyrate, the most potent HDACi produced though colonic fermentation of fibre. In order to determine levels of butyrate and other SCFA, the stool sample collected from patients will be weighed and extracted freshly (within 3 hr of production) using a standard procedure [29] to yield SCFA. The absolute level of levels of each SCFA will be determined by gas chromatography ion collaboration with [name], University of Newcastle upon Tyne. The acetylated proteome will be analysed by a method reported elsewhere ([name] et al., in preparation), modified from a published protocol for analysis of global protein acetylatyion [30]. In brief, tissue samples will be lysed, soluble protein extracted and acetyl proteins immunoprecipitated before separation by 2d gel electrophoresis. Owing to the numbers of biopsies' worth of immunoprecipitate required for a 2d gel (6-8 biopsies), a pooling strategy will be required for the FACT OBS analysis. Patients will be pooled into deciles within pathology groups (i.e. deciles within adenoma group, cancer group, normal group) according to faecal butyrate levels, and all biopsies in each pool will be used for a single 2d gel.

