#### Primary Aims

1. To undertake a cross-sectional study of global protein acetylation profiles in normal subjects and those with colonic polyps and colorectal cancer. This study arm is named FACT OBS.

2. To determine, in the same clinical groups, the relationship between global protein acetylation profile and faecal SCFA levels.

3. To undertake a fibre supplementation study in morphologically normal GI patients and patients with colonic polyps to determine the effect of fibre supplementation on the global acetylation profile. This study arm is named FACT INT.

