#### Patient Recruitment and sample collection

##### FACT OBS recruitment

Recruitment targets were 30 normal, 30 polyp and 30 cancer patients. Patients were primarily recruited via outpatient clinics and through patient databases at Sheffield's Northern General Hospital and Royal Hallamshire Hospital. All patients were attending for diagnostic colonoscopy and patient and researchers were unaware of the diagnosis at time of recruitment and consent. Up to 10 biopsies were collected at endoscopy from these patients. Biopsies were collected with a Radial Jaw 4 2.8 mm forceps (see table 1). Two weeks post-endoscopy, patients were asked to provide a stool sample and completed a Food Frequency Questionnaire (FFQ).

**Table 1 T1:** Position and uses of biopsies taken during endoscopy for the FACT OBS and FACT INT arms of this study.

Site	Biopsies	Purpose

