**FACT OBS**		

Mid-sigmoid	1	Whole mount
	2	Immunohistochemistry
	3	Proteomics
	4	Proteomics

Contralateral	1	Immunohistochemistry
	2	Proteomics
	3	Proteomics

Lesion	1	Immunohistochemistry
	2	Proteomics
	3	Proteomics

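### As written, the FACT OBS gel rule mixes lesion with non-lesion tissue in polyp and cancer pools but not in normal pools, and conflicts with the protocol's own 6-8 biopsies per gel

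*Protocol article*

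**What the plan says.** - **Aim.** Primary Aim 1 is a "cross-sectional study of global protein acetylation profiles in normal subjects and those with colonic polyps and colorectal cancer".
- **Group sizes.** Under FACT OBS recruitment: "Recruitment targets were 30 normal, 30 polyp and 30 cancer patients".
- **Biopsies.** The same section says "Up to 10 biopsies were collected at endoscopy from these patients". Table 1 divides the ten into four mid-sigmoid, three contralateral and three lesion biopsies. Two at each site are for proteomics. The other four are for whole mount or immunohistochemistry. The table does not say which pathology groups give which sites.
- **Why pool.** Under Primary outcome measure, the reason given for pooling in FACT OBS opens: "Owing to the numbers of biopsies' worth of immunoprecipitate required for a 2d gel (6-8 biopsies".
- **How to pool.** "Patients will be pooled into deciles within pathology groups", ordered by faecal butyrate, and "all biopsies in each pool will be used for a single 2d gel". Pathology group and butyrate are the only pooling variables named. Biopsy site is not mentioned.
- **FACT INT.** The section on its pooling strategy says that no pooling is needed there, because more biopsies per patient come from one part of the colon.

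**The concern.** The gel rule covers all the biopsies in a pool and allows one gel. Taken with Table 1, that puts three kinds of tissue on each polyp or cancer gel, one of them lesion. A normal subject has no lesion, so a normal gel cannot contain that tissue. Tissue composition would then differ systematically between the groups that Primary Aim 1 compares.

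The article's hypothesis concerns the state of the colorectal mucosa. If a spot differs between cancer and normal gels, a mixed gel cannot show whether the difference lies in the mid-sigmoid mucosa, in the contralateral mucosa or only in the lesion. The mixing happens before immunoprecipitation and gel separation, so no analysis plan can undo it.

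The rule also does not fit its own rationale. Pooling is justified by the number of biopsies that a gel needs, yet the rule as written gives far more than that number in two of the three groups.

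**Working it through.** **Inputs**
- Patients per group: 30 (FACT OBS recruitment).
- Pools per group: 10 (deciles; Primary outcome measure).
- Proteomics biopsies per patient: mid-sigmoid 2, contralateral 2, lesion 2 (Table 1).
- Biopsies needed per gel: 6-8 (Primary outcome measure).
- Sites sampled in normal subjects: not stated. Mid-sigmoid only is an assumption; mid-sigmoid plus one further non-lesion site is the alternative.

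**Step 1: patients per pool.** 30 / 10 = 3.

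**Step 2: can the 6-8 figure be reproduced?** Biopsies per gel = patients per pool x proteomics biopsies per patient that go on the gel.

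| Reading | Polyp or cancer gel | Normal gel | Within 6-8? |
|---|---|---|---|
| One gel per pool per site | 3 x 2 = 6 | 3 x 2 = 6 | Yes, every group |
| One gel per pool, all sites; normals mid-sigmoid only | 3 x 6 = 18 | 3 x 2 = 6 | Normal only |
| One gel per pool, all sites; normals two sites | 3 x 6 = 18 | 3 x 4 = 12 | No group |

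Only site-separate gels reproduce the figure in all three groups.

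**Step 3: tissue mix under the rule as written.** Lesion share in a polyp or cancer gel: (3 x 2) / 18 = 1/3. Lesion share in a normal gel: 0 under either assumption.

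**Step 4: is pooling of patients needed if sites may be mixed?** One lesion patient gives 2 + 2 + 2 = 6 proteomics biopsies, already inside 6-8, so the polyp and cancer groups would not need it. A normal subject with 2 biopsies would still need pools of 3 under either reading. The mismatch with the rationale therefore concerns the lesion groups.

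**Step 5: illustration of dilution.** Assume equal protein from every biopsy and an F-fold change confined to lesion tissue. The change seen on the mixed gel is (4 + 2F) / 6.
- F = 2: 8/6 = 1.33-fold.
- F = 3: 10/6 = 1.67-fold.

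Conversely, on these assumptions a 1.33-fold difference between groups could come wholly from the lesion third.

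**Step 6: gel counts.**
- As written: 3 groups x 10 pools = 30.
- Mid-sigmoid gels only: 3 x 10 = 30.
- Lesion and contralateral gels in addition: 2 groups x 2 sites x 10 pools = 40, so 70 in all if normals give mid-sigmoid tissue only.

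**Step 7: slack.** With 25 patients in a group, ten pools average 2.5 patients, or 2.5 x 2 = 5 biopsies per site, which is below 6.

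**The case against.** The strongest reply is that site-separate gels were meant all along. The per-site count of 6 falls inside the stated range, while 18 is more than double its upper end. The FACT INT pooling section explains the absence of pooling by the number of biopsies from one part of the colon, which suggests that a gel is meant to represent one region. The laboratory method is also said to be reported elsewhere, and an article gives only a summary of it.

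Much of this stands as evidence of intent. A reader might infer from the gel rule that mixing the sites is the settled plan; the documents do not support so firm a statement. They do support this: the only written rule says all biopsies and one gel, nothing in the article keeps the sites apart, and anyone following the text would mix them. This is a stated rule that disagrees with the figures beside it, not a detail left out.

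Three further inferences are tempting and should not be drawn.
- *That every biopsy goes on the gel.* Table 1 reserves four of the ten for other uses; only the proteomics biopsies are at issue.
- *That site mixing destroys a within-patient comparison of lesion with contralateral tissue.* Pooling patients by decile already removes any within-patient proteomic contrast, and no listed aim names that contrast.
- *That polyp and cancer gels carry three times the protein.* The article does not state the protein load per gel or any normalisation. The 18 against 6 is a count of biopsies, and rests on normals giving mid-sigmoid tissue only.

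**Conclusion.** The point holds as a conflict between the written gel rule and the protocol's own figures, with a serious consequence if the rule is followed literally. Polyp and cancer gels would then hold 18 proteomics biopsies, one third of them lesion. Normal gels would hold 6 or 12, none of them lesion. Pathology would be confounded with tissue site in the Primary Aim 1 comparison, irreversibly once the tissue is mixed.

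The absence of lesion tissue from normal pools needs no assumption beyond the meaning of normal. The normal-pool count does depend on which sites normal subjects give. All counts assume full recruitment of 30 per group and complete biopsy sets. The 1.33-fold and 1.67-fold figures are illustrations that assume equal protein per biopsy and a change confined to the lesion; they are not estimates from the documents.

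Whichever reading was intended, the sentence must be changed, because it governs the primary outcome measure and agrees with the 6-8 range in at most one of the three groups.

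**What to change.** Replace the sentence on gels with:

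> Pools are formed within pathology group and within biopsy site, with one gel per pool per site. Normal, polyp and cancer groups are compared on mid-sigmoid gels only (30 gels). Where lesion and contralateral gels are also run, they are compared within pool.

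Also state in Table 1 which sites are sampled in normal subjects.

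**Cost.** The comparison between groups needs 30 gels, the same number as the rule as written. Lesion and contralateral gels are optional and add up to 40. All of them use tissue already taken, so no extra patients or biopsies are needed.

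**Downside.** Six biopsies per site is the bottom of the 6-8 range. A group that falls short of 30 would need fewer, larger pools than deciles. For example, 25 patients could form seven pools of 3 and one of 4 (7 x 3 + 4 = 25), giving 6 or 8 biopsies per gel but 8 gels for that group instead of 10. The text should allow for this.

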###### Pooling strategy for FACT INT

As larger numbers of biopsies are being taken from a single region of the colon per patient for the FACT INT study, no further pooling will be required.

###### Analysis of gels and difference discovery

The software of choice for analysis, quantitation of 2 d gels and for identification of differences between gels will be Samespots [31].

###### Residual proteome

The residual proteome (i.e. proteins not bound on the acetyl-IP column) will be separated and analysed using an iTRAQ workflow [32] to investigate comprehensively possible differences between the epithelial proteome in response to carcinogenesis and to SCFA.

#### Secondary outcome measures

##### Alteration in crypt cell proliferation in i) carcinogenesis; ii) response to SCFA; iii) in response to elevation of SCFA

Several methodologies/measures are available for assessing crypt cell proliferation rates. These include immunohistochemical approaches on formalin-fixed, paraffin-embedded (FFPE) sections and whole mount analysis. FFPE sections may be probed with a number of antibodies to give a measure of cell proliferation. Antibodies to the Ki67 antigen cross-react with all cells actively in cycle, irrespective of the stage in cell cycle. Some commentators suggest that immunohistochemical approaches are insufficient to measure accurately mitosis as they depend on evaluation within a cross-section whereas mitoses will occur in the 3d structure of the crypt [33]. Whole mount analysis, involving the fixation of biopsies, followed by staining with Feulgen's reagent and scoring mitosis in the full depth of the crypt offers an alternative approach [34].

In this study we will use both Ki67 and whole mount/Felugen's as assays of crypt cell proliferation. Our preliminary findings show correlation between both indices and suggest that Ki67 may be an adequate general index of proliferation [35].

We will assess the relationship between fibre intake, SCFA levels, butyrate levels, associated pathology and each of the proliferation indices in samples collected in the FACT OBS study. We will assess whether differences observed attributed to either fibre/SCFA or pathology can be reverted by elevation of fibre intake and faecal SCFA level with samples collected in the FACT INT study.

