**Methods an design:**

There are two principal arms to this study: (i) a cross-sectional study (FACT OBS) of 90 subjects recruited from gastroenterology clinics and; (ii) an intervention trial in 40 subjects with an 8 week high fibre intervention. In both studies the principal goal is to investigate a link between fibre intake, SCFA production and global protein acetylation. The primary measure is level of faecal butyrate, which it is hoped will be elevated by moving subjects to a high fibre diet. Fibre intakes will be estimated in the cross-sectional group using the EPIC Food Frequency Questionnaire. Subsidiary measures of the effect of butyrate on colon mucosal function and pre-cancerous phenotype will include measures of apoptosis, apoptotic regulators cell cycle and cell division.

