##### FACT INT recruitment

Recruitment target for the FACT INT study is 20 normal and 20 polyp subjects consuming an habitually low fibre diet. Patients will be recruited via the outpatients clinics for the bowel screening programme, Northern General Hospital, Sheffield. The biopsy protocol is summarised in Table 1. Stool samples, FFQ and a four day food diary will be collected circa 2 weeks after the endoscopy. Subjects will be asked to comply with a high fibre diet for an eight week period (including a 2 week ramp phase). Stool sampling and a further food diary will be collected at the end of the 8 week intervention, patients will then return for a second endoscopy with the same biopsying protocol.

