#### Inclusion and Exclusion Criteria

##### Inclusion criteria

Male subjects (FACT OBS only), Aged > 40, Low habitual NSP and RS consumption (FACT INT only), Low level of faecal butyrate BMI 20-29.

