##### Alteration in mucosal apoptosis in i) carcinogenesis; ii) response to SCFA; iii) in response to elevation of SCFA

Animal models have suggested that elevated fibre intake and fermentation alone do not alter levels of background apoptosis in the colon mucosa in rats. There are few if any studies addressing directly whether apoptotic rates are altered in response to fibre intakes/SCFA levels in humans. Several assay methods are available for the scoring of apoptosis, including antibodies to protein cleavage products specifically generated during apotosis. The M30 antibody recognises a neoepitope produced through cleavage of cytokeratin 18, and the CC3 antibody recognises the cleaved, activated form of apoptosis-specific protease caspase 3.

As described above for the proliferation indices, we will assess the relationship between fibre intake, SCFA levels, butyrate levels, associated pathology and apoptositic index in the FACT OBS study and establish wther regression to normality can be achieved through elevation of fibre intakes through the FACT INT study.

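### FACT INT asks whether raised fibre intake reverts differences, but all 40 subjects receive fibre, so before-after change cannot be attributed to fibre

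*Protocol article*

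**What the plan says.** The abstract of the protocol article describes FACT INT as "an intervention trial in 40 subjects with an 8 week high fibre intervention". Under FACT INT recruitment: "Recruitment target for the FACT INT study is 20 normal and 20 polyp subjects consuming an habitually low fibre diet". The same section continues: "Subjects will be asked to comply with a high fibre diet for an eight week period (including a 2 week ramp phase"). The High Fibre intervention section makes no distinction within the arm: "Patients recruited to the FACT INT arm will be offered a range of high-fibre foods". No randomisation, habitual-diet group, crossover or run-in is described.

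Each subject has one endoscopy before and one after the diet. The baseline stool sample and diary are collected about two weeks after the first endoscopy. The final ones are collected at the end of week 8, before the second endoscopy.

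The questions put to this design are causal:

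- The third item under Primary Aims is to determine what effect fibre supplementation has on the acetylation profile.
- The proliferation section will assess whether differences attributed to fibre/SCFA or to pathology "can be reverted by elevation of fibre intake and faecal SCFA level with samples collected in the FACT INT study".
- The apoptosis section will establish whether a return to normal "can be achieved through elevation of fibre intakes through the FACT INT study".
- The Discussion looks ahead to biomarkers shown to be able to return to normal.

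On eligibility, the inclusion criteria list "Male subjects (FACT OBS only"), and the exclusion criteria bar women from FACT OBS only. A low faecal butyrate level is an inclusion criterion that is not tied to one arm and has no cut-off.

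**The concern.** To say that fibre reverted a difference, one needs to know what the marker would have done over the same weeks without fibre. FACT INT never observes that. The normal group does not supply it, because its members also receive fibre; they are a pathology comparator and not a diet control. Nor do the other arms: FACT OBS is cross-sectional, and FACT VAL studies bowel preparation in 6 + 6 patients.

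Other explanations for a shift between visits can be found in the protocol itself. It treats bowel cleansing as a possible influence on the secondary measures, since FACT VAL exists to study it. The two stool samples differ in time since an endoscopy as well as in diet. Selection for low butyrate makes a rise on remeasurement likely even if fibre does nothing.

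The yardstick for normality is a further difficulty. It comes from men in FACT OBS and would be applied to a FACT INT sample that may include women.

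At stake is the meaning of the trial's main message: a drift unrelated to fibre could be reported as reversal of a pre-cancerous phenotype by diet.

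**Working it through.** **The plan's own figures.** The two recruitment targets, 20 + 20 = 40, agree with the abstract. The article states that no data exist for a power calculation, so there is no power figure to reproduce. Everything below is illustration; the shifts, correlations and cut-offs are assumptions.

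**1. What a before-after contrast estimates.** In each group, mean change = drift + fibre effect. With everybody on fibre, these two terms cannot be separated.

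**2. How often a pure drift would be significant.** Paired t-test, two-sided 5%, drift d in SD of within-person change, no fibre effect. The non-centrality is δ = d√n, and power is the chance that a non-central t with n−1 degrees of freedom exceeds the critical value.

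- n=40, d=0.45: δ = 0.45 × √40 = 2.85, critical value 2.02, power 79%. At d=0.454 it is 80%.
- n=20, d=0.45: δ = 0.45 × √20 = 2.01, critical value 2.09, power 48%.
- d=0.32: 51% at n=40 and 27% at n=20.
- For 80% at n=20, d would have to be 0.66.

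The n=20 figures are the relevant ones for reversion of a polyp-related difference, since only the 20 polyp subjects have one to revert.

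**3. Regression to the mean in faecal butyrate.** Assume a normally distributed value, test-retest correlation ρ, entry restricted to the lowest fraction f, and the sample used for entry serving as baseline. With c the f-quantile, the expected rise with no fibre effect is (1−ρ)·φ(c)/f, in between-person SD. For the lowest half, φ(0)/0.5 = 0.399/0.5 = 0.798. The last two columns give how often a paired test shows a significant rise (4,000 simulated studies per setting).

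| ρ | Rise (SD) | n=20 | n=40 |
|---|---|---|---|
| 0.4 | 0.6 × 0.798 = 0.48 | 54% | 85% |
| 0.6 | 0.4 × 0.798 = 0.32 | 35% | 66% |
| 0.8 | 0.2 × 0.798 = 0.16 | 20% | 36% |

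Across other cut-offs at n=40, the range runs from 13% (lowest three quarters, ρ=0.8) to practically 100% (lowest quarter, ρ=0.4).

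**4. What the polyp-minus-normal contrast can do.** (drift + fibre effect in polyp) − (drift + fibre effect in normal) = the difference between the two fibre effects. Shared drift cancels, but so does any shared fibre effect. With 20 versus 20, the detectable difference at 80% power is (1.96 + 0.84) × √(2/20) = 0.89 SD of change, or 0.91 using the t distribution.

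**5. What change-on-change regression can do.** By Fisher's z, the correlation detectable with 80% power at n=40 is tanh(2.80/√37) = tanh(0.460) = 0.43. Partialling out one baseline covariate makes it tanh(2.80/√36) = 0.44. This tests association between changes, not an effect of assigned fibre.

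**The case against.** It can fairly be said that FACT INT is an exploratory biomarker study, that the article condenses a fuller document, and that tests and covariates belong in an analysis plan. That holds for the choice of test. It does not remove the point, because no analysis plan can recover an untreated change that is never measured.

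Several stronger readings are tempting and should be resisted:

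- **That the protocol claims fibre reverts the changes.** It does not. Both secondary-outcome sections pose a question to be assessed, and the Discussion is conditional.
- **That any drift toward normal will be counted as reversion, or that the normal subjects will go unused.** No test is stated. Enrolling both groups under one protocol permits the comparison.
- **That mucosal markers regress to the mean through selection at baseline.** Nobody is selected on a mucosal value, and the reference differences come from a separate sample. The mechanism acts directly on butyrate, and on mucosal markers only as far as they correlate with it.
- **That polyp removal or assay batch differs between visits.** The article says nothing on either. Batching by visit is a risk to prevent, not a stated flaw.
- **That bowel preparation differs between the two visits.** This is not stated; the biopsy protocol is the same at both.
- **That the 80% figure applies to reversion of polyp-related differences.** It applies to all 40 subjects; for the 20 polyp subjects it is 48%.

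**Conclusion.** The concern holds in this form: the design supports a description of change after a high fibre diet, not the determination of fibre's effect or of reversion by fibre. That conclusion follows from the stated design and needs no assumption.

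Its practical size does depend on assumptions. The article gives no figure for drift, for the repeatability of butyrate or for the entry cut-off, so the percentages show what would happen if shifts of those sizes occurred, not that they will. Butyrate carries the extra exposure from selection; the mucosal markers are open to time, repeat endoscopy and preparation. The sex mismatch is a separate, smaller limit on any comparison with FACT OBS reference values.

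Neither the polyp-normal contrast nor the change-on-change regression restores causal attribution. The first loses a common fibre effect, and the second remains observational.

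**What to change.** 1. Restate the FACT INT aims and conclusions (third primary aim, proliferation and apoptosis sections, Discussion) as change after the intervention, without attribution to fibre, whatever the secondary analyses show.
2. Add, as supporting observational evidence, a baseline-adjusted regression of marker change on change in faecal butyrate and in diary fibre intake, stating that about r = 0.43 is detectable with 80% power at n=40.
3. Report change in polyp and normal subjects side by side, noting that their difference removes shared drift but also any shared fibre effect.
4. Process both visits of a subject in the same gel or stain batch, as a precaution.
5. Show the comparison with FACT OBS reference values in men.

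The cost is a weaker causal claim and slightly more batch planning; the samples and diaries are already to be collected. Keeping the causal wording would instead require a concurrent habitual-diet group with the same two assessments. Splitting the present 40 subjects 20 versus 20 for that purpose would detect only about 0.89 SD of change, by the same formula as in step 4 of the working.
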